## 6.2 Description of outcome variables in relation to objectives and hypotheses

The primary variable, transfusion rate, will be measured as the proportion ( $\pi$ ) of patients in each treatment group that is receiving allogeneic blood transfusion of the total number of patients in each treatment group. The hypothesis to be tested is:

$$H_0 = \pi_s = \pi_c$$

versus

$$H_1 = \pi_s \neq \pi_c$$

Where:

$\pi_s$  = Proportion patients treated with Sangvia® that require allogeneic blood transfusion in addition to Sangvia® transfusion.

$\pi_c$  = Proportion patients in the control group that require allogeneic blood transfusion.

The hypothesis will be tested using the Fischer Exact Test. The hypothesis will be rejected if the p-value is  $\leq 0.05$ .

Secondary objectives will be tested using similar hypotheses. The total and variable specific proportion values for infection rate, use of post-operative antibiotics and adverse events will be tested between the groups using the Fischer Exact Test. Continuous variables (e.g. post-op Hb values) will be compared and tested using the Wilcoxon Rank Sum test. Laboratory blood markers will also be evaluated for changes over time within each treatment group and this change will be tested using the Wilcoxon Signed Rank test.

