There are several indications for autotransfusion, i.e. orthopaedic surgery, vascular surgery, liver transplantation, trauma and cardiac surgery. Contraindications to blood salvage include infection and malignant disease. The risks of using autotransfusion are mainly related to blood quality and systemic effects on the patient. One example is high free haemoglobin level in salvaged blood due to haemolysis secondary to surgical trauma, suctioning techniques and vacuum aspiration. The systemic levels of free haemoglobin after autotransfusion are however depending on several factors such as amount of retransfused blood, age, sex and medical status of the patient but the clinically critical plasma levels of free haemoglobin have not been determined. Another risk may be related to the potassium concentration in salvaged blood which is dependent on many factors such as degree of cell haemolysis and time elapsed before transfusion. Also, intra-operatively salvaged blood has a low concentration of fibrinogen and of factors V, VIII and X and processing of blood leads to activation of complement and formation of pro-inflammatory cytokines. Postoperatively shed blood has a high concentration of complement anaphylatoxins as well as IL-1, IL-6 and IL-8. High levels of inflammatory mediators may cause the development of circulatory instability and pulmonary insufficiency but may also reduce immunosuppression after surgery and the risk of

postoperative infections. In contrast to the possible risk of autotransfusion there are also possible benefits. E.g. the leukocyte count in salvaged blood is close to that of normal blood, salvaged red cells show normal morphology in contrast to allogeneic donor cells and the concentration of 2,3-diphosphoglycerate is higher in salvaged blood than in banked blood which is associated with higher oxygen delivery capacity. Today, a widespread experience with blood salvage and autotransfusion exists and the reported complications are few. A recommendation for a limit of 1500 ml in intra-operative use and of 2000 ml in postoperative use is considered to be safe.

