### 2.2 Secondary objectives

The secondary objectives of the study are....

....to observe and compare clinical efficacy by means of postoperative infection rates, use of postoperative antibiotics, length of hospital stay and health status for patients transfused with Sangvia® blood, no blood and/or allogeneic blood.

....to observe and compare clinical efficacy by means of systemic postoperative haemoglobin levels for patients transfused with Sangvia® blood, no blood or allogeneic blood.

....to collect details in health care utilisation (medications, in-patient service use, blood management) that would allow a calculation and comparison of cost-consequences applying either alternative in the blood management and from the perspective of the payer

....to observe and compare safety by means of adverse events, highlighting renal failures and events potentially related to transfusion, body temperature and other clinical complications for patients transfused with Sangvia® blood, no blood or allogeneic blood.

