#### 3.3.3 Exclusion criteria

Any of the following is regarded as a criterion for exclusion from the study:

1. Involvement in the planning and conduct of the study (applies to both Astra Tech staff or staff at the study site).
2. Previous enrolment or randomisation of treatment in the present study.
3. Expected or confirmed participation in another clinical study, that may interfere with the present study, during the study period.
4. Suspected severe non-compliance to protocol as judged by the investigator.
5. Current symptoms of haemophilia.
6. Current symptoms of hyperkalaemia.
7. Current symptoms of systemic infection or local infection in the operation field.
8. Current symptoms of impaired renal function including creatinine/clearance levels above the normal reference values.
9. History of or presence of malignant disease with propensity for systemic spread during the last 5 years.
10. Current or expected use of cytotoxic drugs.

11. Current untreated anaemia (e.g. sickle cell anaemia), i.e. Hb concentration < 11 g/dl (7 mmol/l).
12. Use of recombinant erythropoietin.
13. Use of aprotinin and/or fibrin sealant.
14. Use of other autologous blood transfusion than that with the Sangvia® system (e.g. CellSaver, pre-donation, acute normovolemic haemodilution etc.).
15. Women of childbearing age.
16. Fractures
17. Revision/secondary total hip surgery with expected serious bone grafting

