#### **4.4.1.2 Recording of Adverse Events and Adverse Device Effects**

At each assessment point and/or visit, scheduled or unscheduled, the subject will be asked an open question; "Have you had any health problems since the previous visit?"

All AEs must be recorded in the CRF's AE log:

- Time of onset, action taken, outcome and whether the AE constitutes a SAE or not must be specified for events regarded as "possibly/probably/definitely" related to the device by the investigator.
- A short description and whether the AE constitutes a SAE or not must be specified for events regarded as non-related to the device by the investigator.

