## 6.5 Determination of sample size

The primary variable and objective is the base for the sample size calculation. The sample size formula used is referred to in Lachin 1981.

$$N = \frac{(Z_{\alpha} + Z_{\beta})^2 4\bar{\pi}(1 - \bar{\pi})}{(\pi_s - \pi_c)^2}$$

Where:

N = total number of patients

$Z_{\alpha} = 1.96$  ( $\alpha = 0.05$ )

$Z_{\beta} = 1.2816$  ( $1 - \beta = 0.90$ )

$$\bar{\pi} = \frac{\pi_s + \pi_c}{2}$$

An estimation normal use of allogeneic blood of 21% is based on reported values in the literature. It is acknowledged that in revision surgery a higher percentage of allogeneic blood transfusions is seen than in primary total hip replacements. Because revision patients requiring serious bone grafting are excluded, the percentage of revision patients is expected to be just slightly higher than for the average primary total hip. A high number of revision, e.g. a maximum of 30%, in the total group of patients is considered to have limited effect of the total transfusion rate but are accounted for in the 21% assumed for the total group. The expected values of transfusion rate in the Sangvia® group is estimated to lie around 7%. Accordingly, imputing the values for the estimated transfusion rates in the test and control group generates a mean transfusion rate value of 14%. The sample size necessary for detection of this expected difference in transfusion rate frequency is calculated to 260 patients (5% significance level, two-sided hypothesis, 90% power). Additional 40 patients will be included in the study to compensate for drop-out. In summary, 300 patients will be included in total and 150 in each treatment group.

The transfusion rate of bank blood is considered to vary dependent on type and complexity of surgery. Greatest normal use and differences between the groups are expected in the subgroup with medium (surgery duration 1-2 hours) to complex (surgery duration more than 2 hours) surgery complexity why power are considered to be adequate for the planned subgroup analyses in these groups.

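### The tests stated for creatinine, GFR/creatinine clearance and potassium are nearly blind to large rises in a few patients, so laboratory-only cases that nobody records as adverse events could go uncompared

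*Protocol*

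**What the plan says.** The safety objective (Protocol 2.2) is "to observe and compare safety by means of adverse events, highlighting renal failures and events potentially related to transfusion". The synopsis lists laboratory measurements, among them potassium, creatinine and GFR/creatinine clearance, as safety variables alongside adverse events. They are sampled before surgery, at 3 hours, and on days 1, 2 and 4 (Table 1 and 4.7.1.1). Section 1.1 gives a reason to watch potassium: "Another risk may be related to the potassium concentration in salvaged blood which is dependent on many factors".

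The stated analysis has three parts:
- Section 6.1: number, mean, median, SD, minimum and maximum for continuous data.
- Sections 6.2 and 6.4: Wilcoxon rank sum test between arms for continuous variables.
- Section 6.2, by signed rank test within each arm: "Laboratory blood markers will also be evaluated for changes over time within each treatment group and this change will be tested".

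Adverse event proportions are compared between arms by Fisher's exact test (6.2), and safety conclusions come from the All Patient Treated (APT) set (6.3).

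Cut-offs appear elsewhere. CRP and LPC have post-operative thresholds (4.3.1.1), and renal function has a limit at entry: "Current symptoms of impaired renal function including creatinine/clearance levels above the normal reference values". No post-operative criterion is given for creatinine, GFR/clearance or potassium.

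**The concern.** A renal or potassium harm from reinfused blood would be expected as large changes in a few patients, with the rest of the arm unmoved. The stated tests look for something else. The rank sum test asks whether one arm's values tend to be higher throughout. The signed rank test asks whether values change after surgery within one arm, and makes no comparison between arms.

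Adverse event reporting is the other route. It relies on an open question at each assessment, "Have you had any health problems since the previous visit", together with the investigator's recording of events. The protocol nowhere requires an abnormal laboratory value to be recorded as an adverse event, so a silent rise in creatinine or potassium may be counted nowhere as a case.

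At stake is a statement that renal and potassium values did not differ between arms, resting on tests that would probably miss a several-fold excess of large rises. Section 1 gives confirming earlier safety results as a purpose of the trial.

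**Working it through.** **The plan's own figure.** Section 6.5 uses N = (Zα + Zβ)² · 4π̄(1 − π̄) / (πs − πc)², with 21% v 7%:

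(1.96 + 1.2816)² × 4 × 0.14 × 0.86 / 0.14² = 10.508 × 0.4816 / 0.0196 = 258.2, so 259.

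The plan states "calculated to 260 patients (5% significance level, two-sided hypothesis, 90% power"). This reproduces. It concerns transfusion rate only and gives no assurance about laboratory safety. The inflated figure of 150 per arm is used below.

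**Assumptions, none in the protocol.** 2 to 8% of test patients and 0 to 1% of controls have a large rise. For creatinine: log-SD 0.20 at baseline, log-SD 0.12 for usual change, and a 1.5- to 3-fold rise in affected patients.

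**Rank sum test, by hand.** Suppose every affected value exceeds every unaffected one, which is the most favourable case for the test. The probability that a random test patient exceeds a random control is then 0.5 + (pT − pC)/2. The null standard error is √[(2n + 1)/(12n²)] = √[301/(12 × 150²)] = 0.0334. Two-sided 5% power, both tails:

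| Affected, test v control | Shift from 0.5 | z | Power |
|---|---|---|---|
| 2% v 0% | 0.010 | 0.30 | 6% |
| 5% v 1% | 0.020 | 0.60 | 9% |
| 8% v 1% | 0.035 | 1.05 | 18% |

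The size of the rise does not enter once the ranks are separated, so a larger harm in the same few patients adds no power. Simulation agrees. Shifts of 4 or 8 SD gave about 6%, 9 to 10% and 17 to 19% in these three cases, and the creatinine model gave about 8 to 10% and 17 to 20% in the last two. The median moved by at most about 0.1 SD.

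**Fisher's exact test on a per-patient proportion.** With 150 per arm, 6 v 0 gives p = 0.030 and 8 v 1 gives p = 0.036, while 5 v 0 gives p = 0.060 and 7 v 1 gives p = 0.067. Simulated power under the creatinine model:

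| Case definition | 5% v 1% | 8% v 1% |
|---|---|---|
| Rise of at least 1.5-fold from own baseline | 37–40% | 76–80% |
| Crossing the upper reference limit, entry below it | 12–21% | 30–52% |

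The second row depends on where the limit lies and how many samples count. At 8% v 1% it reaches about 57% with the limit 3 SD above the baseline mean. It is weaker because ordinary fluctuation carries unaffected patients over the line. With the limit at the 97.5th percentile of baseline, about 4 to 9% of controls cross.

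**Very few cases.** At 2% v 0%, Fisher's test reaches only about 9% even when affected patients are identified perfectly.

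**What the planned maximum shows.** At a 2% rate, the chance of at least one case among 150 is 1 − 0.98¹⁵⁰ = 95%. The maximum would probably show that a case exists, but it describes one patient per arm and cannot distinguish 1 case from 12.

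**The case against.** A reader might infer that renal failure itself would escape the analysis. The protocol does not support that. The objective assesses renal failure through adverse events, section 6.2 compares event proportions by Fisher's exact test, and section 6.3 bases safety conclusions on all patients. The adverse event definition in 4.4.1.1 is also broad enough for an investigator to record a laboratory abnormality; it simply does not require it.

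Nor are the markers summarised only by centre and rank, because section 6.1 also plans minimum and maximum. Hyperkalaemia is not named in the objective; potassium comes from the background.

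Threshold and shift tables are often left to a SAP. Section 6.1 says one may be prepared, and none is shown, so their absence alone would be no finding. What stands is that the protocol itself names the tests for these markers, and those tests suit this kind of harm poorly.

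A tempting remedy is to count every crossing of a reference limit as new, since abnormal patients are excluded at entry. That fails for potassium: section 3.3.3 excludes only symptoms of hyperkalaemia, and the screening step in 3.1 verifies haemoglobin and creatinine/clearance, not potassium. For creatinine, crossing the limit also loses much of the power gain, as the second table shows.

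**Conclusion.** The point holds in a limited form. For creatinine, GFR/clearance and potassium, the stated between-arm test has about 8 to 20% power against an excess of 5 to 8% v 1% of patients with large rises, at 150 per arm. The stated within-arm tests cannot compare arms at all. What may be missed is confined to laboratory-detected renal impairment or high potassium that is not recorded as an adverse event.

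The rank sum result needs only the assumed rates. The gain from a proportion also rests on the assumed creatinine variability and the 1.5-fold definition: it is substantial at 8% v 1%, moderate at 5% v 1%, and mainly descriptive near 2% v 0%. Potassium was not simulated. Its proposed rule is a crossing rule, so its power is likely to resemble the lower row of the second table.

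**What to change.** In sections 6.2 and 6.4 add, on the APT set and by arm, the number and percentage of patients with:
- a pre-specified relative rise in creatinine, or fall in GFR/clearance, from their own screening value at any post-operative sample;
- potassium above the laboratory's reference range at any post-operative sample when it was not above it at screening.

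Compare arms by Fisher's exact test with a confidence interval for the difference, and report the result beside the renal adverse events. The interval matters most when cases are few, because it shows how large an excess remains possible. State that the cut-offs are for analysis only and set no rule for patient care. The 1.5-fold value used in the working is an illustration; the sponsor should fix the value before seeing data by arm.

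The signed rank tests may stay as description but should not support a between-arm safety conclusion.

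The cost is one sentence, a few table rows and a cut-off agreed in advance, with each laboratory's potassium limit on file. No new data are needed. A few flagged patients should be expected in both arms.

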## 6.3 Description of analysis sets

The study will be analyzed using a Per Protocol (PP) and an All Patient Treated (APT) approach. Subjects fulfilling the inclusion criteria but none of the exclusion criteria and have been treated according to the protocol without any major deviations (e.g. wrongful transfusion decision of bank blood) will be included in the PP analysis set. All patients will be included in the APT analysis set. Treatment efficacy related conclusions will be based on the results from the PP analysis and demography and treatment safety related conclusions will be based on the results from the APT analysis.

Subgroup analyses of type (primary and secondary) and complexity (easy < 1 hour, medium 1-2 hours and complex > 2 hours) of surgery will be performed as well as analyses per clinic and per blood transfusion type (none, autologous, allogeneic and combinations).

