#### **Transfusion triggers**

| Haemoglobin concentration    | Clinical symptoms                                                                       |
|------------------------------|-----------------------------------------------------------------------------------------|
| ≤ 8.5 g/dl
(≤5.3 mmol/l)* | -                                                                                       |
| > 8.5 g/dl
(>5.3 mmol/l)* | Signs of anemia as deemed by the investigator, e.g. tachycardia and/or hypotension etc. |

\*1 g/dl = 0.6206 mmol/l

Bank blood transfusion can be given to the test group as an addition to the autologous blood using the same transfusion triggers and clinical considerations as in the control group. All bank blood transfusion will be based on transfusion triggers and determined by an assessor unaware of the treatment group whenever possible and the reason/s for the transfusion will be registered. For cases when the decision of bank blood transfusion are taken by a responsible investigator aware of the treatment allocation, e.g. in an emergency situation during surgery, the registered reasons for transfusion will be reviewed by an independent assessor/committee who are unaware of the treatment allocation. Inconsistency in transfusion decision between the

independent assessor/committee and the responsible investigator will be reflected in the per protocol analysis where patients with suspected biased transfusion decisions will be excluded.

To ensure equal distribution of primary and secondary total hip surgery in the test and control group patients will be stratified for this before randomisation, see Figure 1.

All patients will be followed during their hospital stay and at 2 months after discharge.

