### Primary variable

The choice of the primary variable for efficacy is based upon reported findings in the literature.e.g.6,14,40,41 Need for allogeneic blood transfusion is considered to best reflect the blood loss and transfusion frequency in a patient population while other potential primary variables such as length of hospital stay and post-operative haemoglobin values are multi-factorial dependent on for example preferences of the clinic and gender of the patient etc.

The comparison between the treatment alternatives may be biased as it is almost impossible to blind the study. To mitigate the risk of bias the decision of bank blood transfusion will be taken based on transfusion triggers by an assessor unaware of the treatment group whenever possible and the reason/s for the transfusion will be registered. For cases when the decision of bank blood transfusion are taken by a responsible investigator aware of the treatment allocation, e.g. in an emergency situation during surgery, the registered reasons for transfusion will be reviewed by an independent assessor/committee who are unaware of the treatment allocation. Inconsistency in transfusion decision between the independent assessor/committee and the responsible investigator will be reflected in the per protocol analysis where patients with suspected biased transfusion decisions will be excluded. Also post-operative haemoglobin values will be monitored during the study period. In this way systematically inadequate and/or absent allogeneic blood transfusion decisions will be disclosed and addressed during monitoring visits and concerned patients can be excluded from the Per Protocol analysis.

Bleeding volume or complexity of surgery, i.e. surgery time, are considered to possibly influence outcome of the primary variable why stratification for either primary or secondary/revision hip surgery will be made at each recruiting clinic to ensure equal distribution in the two groups. Subgroup analyses of type (primary and secondary) and complexity (easy < 1 hour, medium 1-2 hours and complex > 2 hours) of surgery are planned to further investigate the correlation between the primary outcome and these factors. Age is also a factor that may have an impact on the outcome of the primary variable. It is however considered that randomization as such will ensure approximately equal age distribution in the two treatment groups. Differences in age

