#### 3.3.5.3 Procedures for handling incorrect enrolled subjects

Subjects not meeting the inclusion/exclusion criteria for a study should, under no circumstances, be enrolled into the study - there can be no exceptions to this rule. Incorrect enrolled subjects will

not be included in the per protocol analysis set or in the efficacy conclusions and no financial compensation will be given for these subjects.

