### 3.6 Blinding and procedures for unblinding the study

#### 3.6.1 Methods for ensuring blinding

It is not possible to double blind this study due to the fact that it will be obvious for the study site team to which group the patient has been allocated. I.e. patients in the test group will have their blood collected with the Sangvia® device and in the control group no autologous blood salvage will be performed. The decision of blood bank transfusion will however be assessed in a blinded fashion with an independent assessors unaware of the patient treatment allocation. I.e. each decision of bank blood transfusion will be taken based on transfusion triggers by an assessor unaware of the treatment group whenever possible and the reason/s for the transfusion will be registered. For cases when the decision of bank blood transfusion are taken by a responsible investigator aware of the treatment allocation, e.g. in an emergency situation during surgery, the registered reasons for transfusion will be reviewed by an independent assessor/committee who are unaware of the treatment allocation. Inconsistency in transfusion decision between the independent assessor/committee and the responsible investigator will be reflected in the per protocol analysis where patients with suspected biased transfusion decisions will be excluded. Laboratory sample analyses will be done by assessors unaware of the patient treatment allocation.

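### Efficacy conclusions rest on a Per Protocol set whose membership depends partly on judgements, made after randomisation, about the primary outcome event

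*Protocol*

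**What the plan says.** Protocol section 6.3 defines two analysis sets, Per Protocol (PP) and All Patient Treated (APT). All patients enter APT, but APT supports only the demography and safety conclusions. For efficacy: "Treatment efficacy related conclusions will be based on the results from the PP analysis". Patients treated "without any major deviations (e.g. wrongful transfusion decision of bank blood) will be included in the PP analysis set".

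The protocol describes three ways out of PP that matter here:

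- **Committee review** (sections 3.1, 3.2 and 3.6.1). When an investigator who knows the allocation decides on bank blood, "the registered reasons for transfusion will be reviewed by an independent assessor/committee who are unaware of the treatment allocation". Where the two disagree, "patients with suspected biased transfusion decisions will be excluded".
- **Haemoglobin monitoring** (section 3.2, Primary variable). Decisions found to be systematically inadequate or absent are taken up at monitoring visits, and "concerned patients can be excluded from the Per Protocol analysis".
- **Eligibility failure** (section 3.3.5.3). Wrongly enrolled subjects will "not be included in the per protocol analysis set or in the efficacy conclusions".

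Section 6.2 defines the primary variable as the proportion "of patients in each treatment group that is receiving allogeneic blood transfusion of the total number of patients in each treatment group". Section 3.6.1 accepts that the site team will know each patient's allocation.

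**The concern.** The trial tests for a difference between arms in the proportion of patients given bank blood. Randomisation protects that comparison only while patients stay in the analysis whatever happens to them afterwards. Here, whether a patient stays depends partly on a later judgement about the very decision that produces the outcome.

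The committee route works in one direction. It starts from a transfusion that was given and from the reasons recorded for it. A patient removed by this route is therefore always a patient with the event, and the removal takes one from the numerator and one from the denominator. A non-transfused patient whose missing transfusion is questioned can leave only after haemoglobin monitoring, or for some other major deviation or ineligibility.

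Decisions by an aware investigator, such as emergencies during surgery, need not be equally common in the two arms, nor be disputed equally often. If they are not, removal can create an apparent effect or hide a real one. The conclusion at stake is the trial's main one.

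**Working it through.** **The plan's own figure.** Inputs from section 6.5: control rate 21%, test rate 7%, mean rate 14%, Zα = 1.96, Zβ = 1.2816.

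N = (1.96 + 1.2816)² × 4 × 0.14 × 0.86 / 0.14² = 258.2, which agrees with the stated 260. Adding 40 for drop-out gives 300, or 150 per arm. The sample size is not in dispute.

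**How removal moves the observed rate.** If a fraction f of the transfused patients in an arm of n = 150 with true rate p is removed, the expected PP rate is about

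np(1 − f) / (n − npf).

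With p = 21% there are 0.21 × 150 = 31.5 expected events:

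- f = 10%: 28.35 / 146.85 = 19.3%
- f = 20%: 25.2 / 143.7 = 17.5%
- f = 30%: 22.05 / 140.55 = 15.7%

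The 20% case removes 6.3 patients and the 30% case 9.45.

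**What this does to the test.** Trials were simulated with 150 per arm and the two-sided Fisher exact test at 0.05. Each transfused patient was removed with an arm-specific probability. The protocol gives no expected removal rate, so every fraction below is an assumption. Figures are rounded, because separate runs differ by about one percentage point.

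Type I error, no true effect:

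| Removed, control | Removed, test | 14% in both arms | 21% in both arms |
|---|---|---|---|
| 0% | 0% | 3–4% | 3–4% |
| 0% | 10% | about 5% | about 6% |
| 0% | 20% | about 8% | about 10% |
| 0% | 30% | about 15% | about 19–20% |
| 20% | 20% | about 4% | about 4% |

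Power at 21% versus 7%:

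| Removed, control | Removed, test | Power |
|---|---|---|
| 0% | 0% | 93% |
| 10% | 0% | about 88–89% |
| 20% | 0% | about 77–78% |
| 30% | 0% | about 62% |
| 20% | 20% | about 89% |

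**After the change.** With all 150 per arm kept, Fisher power at 21% versus 7% is 93.1% and type I error at 21% in both arms is 3.6%. The planned 300 patients therefore already support the all-patient analysis at more than the intended 90% power.

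**The case against.** The protocol has a real defence. It admits that the comparison may be biased and sets up a blinded review to deal with it. Decisions are to be taken by a blinded assessor where possible, so only a subset reaches the committee. The ground for removal is a decision judged wrongful, not the receipt of blood as such. A blinded committee has no obvious reason to remove 30% of events from one arm and none from the other, and with modest or equal removal the type I error stays near nominal. All of this stands, and it limits the likely size of the bias. It does not remove the cause: blinding the committee does not equalise how often unblinded transfusions arise in each arm, and deleting the patient discards a randomised outcome even when the judgement is sound.

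Three stronger readings are tempting, and the documents do not support them.

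- *The randomised comparison is lost.* It is demoted. Section 6.3 has APT analysed as well; the efficacy conclusion simply does not rest on it.
- *Only transfused patients can be removed.* That holds for the committee route alone. Section 3.2 also covers absent decisions, and sections 3.3.5.3 and 6.3 remove patients for ineligibility or other major deviations whether or not they were transfused. The net bias can therefore go either way.
- *The two arms have different denominators.* Section 6.2 words the test-arm proportion as "Proportion patients treated with Sangvia® that require allogeneic blood transfusion in addition to Sangvia® transfusion", which could be read as covering only patients who received Sangvia blood. The opening sentence of the same section, and section 4.2.1.2, use the total number of patients or subjects, and sections 3.1 and 3.4.2 have collected blood returned as routine. The phrase is best read as loose description.

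**Conclusion.** The point holds as a design fault. The efficacy conclusion of a superiority trial should not rest on a set from which patients are removed because of a judgement about their outcome event. Nothing elsewhere in the protocol cures this, and an analysis plan could not reverse the stated role of PP without contradicting section 6.3.

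The size is uncertain, because it turns on the difference in removal between arms. If 10% of transfused patients are removed from one arm only, type I error is barely above nominal. At 20% to 30% it is roughly two to six times the 3–4% seen without removal, and the same fractions removed from control alone cost about 15 to 31 points of power (93% less 78% or 62%). Equal removal of 20% costs about 4 points of power and does not inflate type I error materially. These figures assume that removal acts only on transfused patients; removal of non-transfused patients through monitoring is not modelled.

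**What to change.** In section 6.3, base efficacy conclusions on all randomised patients who undergo surgery, analysed in the arm assigned, counting every allogeneic transfusion whether or not the decision was disputed. Patients who drop out before surgery are replaced under section 6.1.3 and may have no transfusion outcome; report their number by arm.

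Keep PP as a sensitivity analysis, with the number and reason of exclusions shown by arm. Add a second sensitivity analysis in which the blinded committee's decision replaces the disputed one and the patient stays in. This uses the same review without deleting anyone.

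As a clarification only, reword the test-arm proportion in section 6.2 to match that section's opening sentence, so that both proportions run over all patients in the group.

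Cost: an amendment to the wording, with no additional patients. Patients who withdraw after surgery but before discharge need a stated rule for how they count, since section 3.3.5.2 asks only for the reason and adverse events. The drawback is that the estimate will include disputed transfusions, and it may be larger or smaller than the PP estimate.
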